##### Qualitative data

An *ethnographic observation* of the local implementation of the SUPPORT program will be performed by social sciences researchers ([name], MV, and [name]) to collect in-depth observational data on the implementation of the program. The observation will notably focus on the reaction of the professionals exposed to PUS, and how they manage and experience the implementation of the SUPPORT program. The interactional processes between professionals delivering the program will also be examined.

For each intervention, five exposed professionals will be randomly selected to participate in an *individual semistructured interview* at the end of the program. The semistructured interviews will last between 30 and 60 min and will be performed by one or two social researchers ([name], MV, and [name]) in the workplace of participants. The participants will be interviewed regarding their individual experience of the SUPPORT program, including: how they perceived the program for themselves and for their team, which mechanisms led to its effectiveness and how the program could be improved. The content of the interview will be recorded and anonymized.

An *activity analysis* will be performed with the providers of the intervention. An activity analysis is an effective means to analyze complex processes occurring in professional practices (e.g., professionalization processes, interactions between professionals, internalization of professional identities, etc.) (Bedny and Karwowski, 2004). We will use the methodology of auto- and allo-confrontation (Mollo and Falzon, 2004). Regarding methodological issues, in auto-confrontation, subjects are confronted with their own activity, whereas in allo-confrontation they are confronted with an activity that they practice but which is performed by someone else. Regarding purpose issues, auto-confrontation aims to reveal the cognitive processes underlying the activity, whereas allo-confrontation allows subjects to develop their knowledge by becoming aware of other types of representations (Mollo and Falzon, 2004). To perform the activity analysis, the providers of the program will be filmed during their intervention in the institution (stage 2 of the SUPPORT program). In auto-confrontations, they will be asked to comment on and to express their experience with and feelings about moments of their intervention. In allo-confrontation, the comments will be made by other providers from the CSP to enrich the discussion about professional practices and question the different ways of running the intervention.

##### Estimated number of participants

The inclusion of 150 exposed professionals is expected for the collection of quantitative data. Considering the five local implementations of the SUPPORT program throughout the SUPPORT-S study, the inclusion of 150 exposed professional is needed to observe a 30% decrease in the mean IES-R score between T0 and T1 with a 90% statistical power.

Of them, a total of 25 professionals will participate in the semistructured interviews. According to previous qualitative studies on professionals’ experiences of adverse events in which similar (Ullström et al., 2014; Ferrús et al., 2016) or lower (Chan et al., 2018; Kable et al., 2018) samples were included, the inclusion of 25 professionals in semidirected interviews should provide sufficient saturation for the representativeness and reliability of the data. However, the sample of participants in semidirected interviews could be increased if saturation is not reached.

#### Data Analysis

The quantitative and qualitative data collected in the study will be separately analyzed through independent statistical and qualitative analyses.

##### Quantitative analysis

Data manipulation and analyses will be performed using R software (R 3.4.1). Qualitative variables will be summarized using numbers and percentages, and quantitative variables will be described using either means and standard deviations or medians and interquartiles. Quantitative variables will be analyzed with the appropriate test, depending on the application conditions. The evolution between T0 and T1 of the following four dependent variables will be measured: (1) PTSD reaction (IES-R > 24), (2) high emotional impact (DES-IV > 108), (3) negative professional impact (e.g., the presence of at least three items indicating negative impact on professional practice or self-efficacy), and 4) low perceived social support (P3SP < 12). For each variable, the total scores will be compared between T0 and T1 using paired Student’s *t*-test or non-parametric sum rank test for matched samples, depending on the distribution of the variables. Then, the proportion of subjects above the cut-off scores will be compared between T0 and T1 using the McNemar test. For the main outcome criteria analysis (IES-R score) a multivariate analysis will be conducted using a multivariate linear mixed model to adjust for main confounders: age, gender, profession, relationship with the decease. All tests will be two-tailed and the statistical significance threshold will be set at 5%.

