##### Quantitative data

A collection of individual quantitative data will be performed before (T0) and after (T1) the SUPPORT program among professionals exposed to a PUS. Sociodemographic data and information on the therapeutic relationship with the deceased will be collected at T0. A pre/post measure of emotional, traumatic and professional impacts and perceived social support will be performed at T0 and T1.

The following sociodemographic characteristics of participants will be collected at T0: age, gender, profession, and years spent working in the organization.

The following information on the relationship between the professional and the event or the patient or user who died by suicide will be collected at T0: connection with the deceased, discovery of the corpse, resuscitation techniques used, being at work or not the day of the event, and therapeutic alliance with the deceased.

The traumatic impact will be assessed at T0 and T1 through the French version of the *Impact of Event Scale-Revised* (IES-R; Horowitz et al., 1979; Weiss and Marmar, 1997; Brunet et al., 2003). The IES-R is a 22-item self-report questionnaire assessing intrusion, avoidance and hyperarousal symptoms in the previous seven days before completion. Each item is rated on a 5-point Likert scale ranging from 0 (not at all) to 4 (extremely), for a total score of 88. According to previous literature, we will retain a cut-off score of 24/88 to indicate a significant traumatic reaction (Bienvenu et al., 2013) and a cut-off of 34/88 for PTSD (Asukai et al., 2002). The French version of the IES-R shows a good internal consistency (alpha coefficients ranging from 0.81 to 0.93) and satisfactory test-retest reliability (correlations coefficients ranging from 0.71 to 0.76) (Brunet et al., 2003).

The emotional impact will be obtained at T0 and T1 through the French version of the *Differential Emotions Scale IV* (DES-IV; Ricard-St-Aubin et al., 2010). The DES-IV is a 36-item questionnaire assessing the level of expression of the twelve following emotions: interest, joy, surprise, anger, contempt, disgust, sadness, fear, guilt, shame, shyness, and self-hostility. The emotions are measured through a 6-item Likert scale ranging from 1 (rarely or never) to 5 (very often), for a total score ranging from 36 to 180. The DES-IV shows good temporal stability (correlations coefficients ranging from 0.49 to 0.79) (Ricard-St-Aubin et al., 2010).

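### The binary IES-R outcome carries a PTSD label at a cut-off of 24, which the protocol's own measurement section assigns to a milder state; it keeps 34 for PTSD

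*Protocol article*

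**What the plan says.** Two sections of the protocol article define thresholds on the same scale.

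- **Quantitative data** (under Data Collection) describes the IES-R as 22 items, and says "Each item is rated on a 5-point Likert scale ranging from 0 (not at all) to 4 (extremely), for a total score of 88". It then states that "we will retain a cut-off score of 24/88 to indicate a significant traumatic reaction" "and a cut-off of 34/88 for PTSD". Each cut-off is tied to its own source and its own meaning.
- **Quantitative analysis** (under Data Analysis) lists four dependent variables. The first is "1) PTSD reaction (IES-R > 24". Total scores are compared first; after that, "the proportion of subjects above the cut-off scores will be compared between T0 and T1 using the McNemar test".

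The value 34 does not appear in the analysis section, and nothing in the article explains why the PTSD name sits on 24 there.

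**The concern.** A reader who takes the definitions from the measurement section expects a PTSD proportion to mean scores at the 34 cut-off. An analyst who follows the analysis section will produce a PTSD proportion from scores above 24. The two groups differ by everyone in the band between the cut-offs.

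At stake is what the published percentages describe. One secondary objective is to give more insight into the consequences of patient or user suicide for professionals. A proportion with a diagnostic name, counted at the threshold for a milder state, would overstate how common PTSD is at T0 and again at T1, judged by the protocol's own definition. A T0 to T1 change in that proportion would also be read as a change in PTSD when it is a change in something else.

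**Working it through.** **Inputs from the article.** Scale: 22 items scored 0 to 4, so the maximum is 22 × 4 = 88, which agrees with the stated total. Analysis cut-off: above 24, with a PTSD label. Measurement cut-offs: 24 for a significant traumatic reaction, 34 for PTSD. Expected number of professionals: 150. The article gives no IES-R mean, SD or distribution and no expected proportion, so there is no stated proportion to reproduce.

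**Step 1: the definitions side by side** (34 read as inclusive).

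| IES-R score | Quantitative data section | Quantitative analysis section |
|---|---|---|
| below 24 | below both cut-offs | negative |
| exactly 24 | depends on whether the cut-off is inclusive (not stated) | negative |
| 25 to 33 | significant traumatic reaction, not PTSD | positive, under a PTSD label |
| 34 to 88 | PTSD cut-off met | positive, under a PTSD label |

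If 34 is read as exclusive, the disputed band becomes 25 to 34.

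**Step 2: direction.** Everyone scoring 34 or more also scores above 24. Hence P(score > 24) = P(score ≥ 34) + P(25 ≤ score ≤ 33) ≥ P(score ≥ 34) for any distribution, at T0 and at T1. The inequality is strict as soon as one participant falls in the band.

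**Step 3: size, under assumptions.** Assume a beta-binomial score on 0 to 88 with mean m and standard deviation SD. Put μ = m/88 and ρ = [SD²/(88μ(1−μ)) − 1]/87; the beta parameters are then μ(1/ρ − 1) and (1−μ)(1/ρ − 1). For m = 20 and SD = 15: 88μ(1−μ) = 15.45, ρ = (225/15.45 − 1)/87 ≈ 0.156, and the parameters are about 1.23 and 4.19.

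| Assumed mean / SD | P(> 24) | P(≥ 34) | Ratio | Gap (points) | Of 150 |
|---|---|---|---|---|---|
| 10 / 18 | 15.2% | 11.2% | 1.36 | 4.0 | 23 vs 17 |
| 15 / 10 | 16.8% | 5.5% | 3.08 | 11.4 | 25 vs 8 |
| 20 / 15 | 33.0% | 18.6% | 1.78 | 14.4 | 49 vs 28 |
| 25 / 15 | 46.1% | 27.2% | 1.70 | 18.9 | 69 vs 41 |
| 30 / 10 | 69.0% | 35.1% | 1.97 | 33.9 | 104 vs 53 |

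These rows include the extremes of a grid with means 10, 15, 20, 25 and 30 and SDs 10, 15 and 18. Over the whole grid the ratio runs from about 1.4 to 3.1 and the gap from 4 to 34 percentage points.

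**Step 4: the paired test.** McNemar counts people who cross the threshold between T0 and T1. Someone going from 36 to 28 crosses 34 but not 24; someone going from 26 to 22 crosses 24 but not 34. The two tests use different discordant pairs, so a result at 24 says nothing certain about change at 34, in either direction.

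**Step 5: what does not use the cut-off.** The total-score comparison and the linear mixed model use the IES-R score itself. The sample size rests on the mean: 150 professionals are "needed to observe a 30% decrease in the mean IES-R score between T0 and T1 with a 90% statistical power". None of the three involves 24 or 34.

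**The case against.** The strongest reply is that this is loose naming and no more. The analysis section speaks of a PTSD reaction, and 24 is a threshold that the measurement section does retain, for a traumatic reaction. On that reading the variable and its test are right and only the name is wrong. This is plausible, and it is why renaming alone removes the contradiction. It does not rescue the text as it stands: the measurement section keeps the PTSD name for 34, so a report that carries the label forward would contradict its own methods.

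A second reply is that the main results are untouched. That stands in full. The main outcome criterion is the IES-R score, effectiveness is itself a secondary objective, and the same threshold applies at T0 and T1, so McNemar at 24 is a sound paired test of the state that 24 denotes.

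A third is that leaving 34 out of a condensed analysis paragraph is no error, because a fuller protocol or analysis plan may use it. That also stands. The absence of 34 is not the fault; the PTSD label on 24 is.

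**Conclusion.** The point holds as an internal contradiction in the label of a binary outcome. The reported PTSD proportions at T0 and T1 would include people whom the measurement section does not class as PTSD. The direction follows from the definitions alone. The factor of about 1.4 to 3.1 rests entirely on assumed beta-binomial scores with means of 10 to 30 and SDs of 10 to 18, and should be read as an illustration.

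Three stronger readings are tempting, and the article does not support them:

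- **That the reported PTSD proportion would be about double the proportion at 34.** Some assumed distributions give this and others do not; no IES-R mean or SD is stated.
- **That the programme would look more effective than it is.** The label shifts the level at both time points, and its effect on the T0 to T1 comparison cannot be determined.
- **That the analysis of the main outcome is faulty.** It uses the score, not the cut-off.

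Severity is moderate: wrong as written, confined to one binary outcome, and correctable before analysis.

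**What to change.** In the Quantitative analysis section, rename the outcome at 24 as significant traumatic reaction, so that it matches the Quantitative data section. Attach any PTSD-labelled proportion only to the stated 34 of 88 cut-off. That proportion may be added as a separately labelled descriptive or secondary dichotomy, but it is not needed to remove the contradiction. If it is added, state its status beforehand, because a further test at 5% is otherwise one more chance of a nominally significant result.

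Use the same inequality in both sections. The analysis section uses strictly greater than, while the measurement section does not say whether a score equal to the cut-off counts.

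The cost is one or two lines of text and, if the 34 dichotomy is reported, one extra paired 2 × 2 table. No new data are needed, and the sample size and main model do not change. Settling it before the data are analysed also removes the option of choosing the threshold after seeing the results.

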#### Stage 3: Late Detection and Counseling

The third stage of the program seeks to perform late detection and counseling support for professionals who are strongly affected or traumatized by exposure to PUS. Those who feared attending the team-based intervention stage may notably receive individual debriefing during this stage. Stage 3 aims to promote the return to normal functioning in the institution, at both the individual and organizational levels. When stage 3 has not been effective in ensuring the recovery among professionals, a fourth stage can be added to properly support the impacted team.

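### All four outcomes are tested only on staff with both T0 and T1 records; a likelihood-based mixed model on all available records would guard against loss related to T0 score at little cost

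*Protocol article*

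**What the plan says.** The Quantitative data section sets two measurement times for every domain: "A pre/post measure of emotional, traumatic and professional impacts and perceived social support will be performed at T0 and T1". The Quantitative analysis section then names the tests.

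- **Total scores of IES-R, DES-IV, professional impact and P3SP:** "For each variable, the total scores will be compared between T0 and T1 using paired" Student's t-test, or a matched rank test, depending on distribution.
- **Cut-off versions of the same four:** "the proportion of subjects above the cut-off scores will be compared between T0 and T1 using the McNemar test".
- **IES-R only:** "For the main outcome criteria analysis (IES-R score) a multivariate analysis will be conducted using a multivariate linear mixed model", whose stated purpose is "to adjust for main confounders: age, gender, profession, relationship with the decease".

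No model is named for DES-IV, professional impact or P3SP. For IES-R, the article does not say whether T0 and T1 both enter the model as outcomes, or which random effects it has. It gives no expected T1 loss rate.

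**The concern.** A paired t-test, a matched rank test and a McNemar test each need both records, so as written a professional who answers at T0 but not at T1 contributes nothing. The complete-pair mean change estimates the change in the whole exposed team only if non-return is unrelated to the change a person would have shown. People with extreme T0 scores tend to change more, simply through regression to the mean. If non-return is related to the T0 score, the complete-pair change is therefore shifted.

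The study has no control group, so the pre/post change is the whole quantitative effect estimate and no comparison arm can offset such a shift. The plan already contains a class of model that could use the unpaired T0 records, but it names that model for one outcome and for another purpose.

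**Working it through.** **The plan's own figure.** The article gives 150 professionals for a 30% fall in mean IES-R at 90% power. The T0 mean, SD and T0-T1 correlation are not given, so 150 can be neither reproduced nor refuted. At two-sided 5%, 150 complete pairs correspond to a standardised paired change of (1.960 + 1.282)/√150 = 0.265. Nothing below contradicts that figure.

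**Bias formula.** Take scores in SD units, with equal SD at T0 and T1, T0-T1 correlation rho and true mean change delta. Given the T0 score, the expected change is delta − (1 − rho) × (T0 score − T0 mean). If a share f is lost and those lost average d SD above the T0 mean, completers average f × d/(1 − f) below it. Hence

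bias in mean change = (1 − rho) × f × d/(1 − f).

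**Inputs.** All of f, d and rho are assumptions; the documents give none of them.

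*Scenario A: f = 0.2, d = 1.* The completers' T0 shift is 0.2 × 1/0.8 = 0.25 SD.

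| rho | bias (SD) |
|---|---|
| 0.3 | 0.7 × 0.25 = 0.175 |
| 0.5 | 0.5 × 0.25 = 0.125 |
| 0.7 | 0.3 × 0.25 = 0.075 |

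*Scenario B: f = 0.2, d about 0.7, rho = 0.5.* The bias is 0.5 × 0.25 × 0.7 = 0.0875, about 0.09 SD.

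**Simulation.** n = 150, 4000 runs, true change −0.30 SD, rho = 0.5, with the log-odds of loss rising by 1 per T0 SD. At 20% loss, those lost average 0.69 SD above the T0 mean, so this row is scenario B and not scenario A.

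| T1 loss | complete pairs | likelihood estimate, all T0 records |
|---|---|---|
| 10% | −0.25 | −0.30 |
| 20% | −0.21 | −0.30 |
| 30% | −0.17 | −0.30 |

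At 20% loss the spread of the two estimates across runs was almost the same, about 0.09 SD each. The simulation makes loss depend on T0 only, which is the condition under which the likelihood estimate is valid. It shows what is gained under that condition and does not show that the condition holds.

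**If loss is completely at random.** Both estimates are unbiased. Over correlations 0.3 to 0.7 and losses of 20% to 40%, the likelihood estimate reduces variance by about 3% to 14%.

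**Direction.** On a distress-type score, losing the worse-off (d > 0) makes the improvement look too small. Losing the little-affected (d < 0) makes it look too large by the same formula.

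**The case against.** The strongest objection is that all the harm comes from missing T1 records, on which the article is silent. Missing-data handling is commonly left to a fuller protocol or SAP, and paired tests can be run on imputed data. This stands in part: complete-case analysis follows from the named tests and is not stated in words, and with full T1 return the bias is zero. But the tests are named, the mixed model is named for one outcome only, and choosing a better named method is a point about the analysis the article fixes.

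Three stronger readings are tempting and are not supported.

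- **That the protocol itself expects the most affected staff to be lost.** The Stage 3 section mentions "Those who feared attending the team-based intervention stage", but this concerns missing a group session, and the sentence goes on to offer those staff an individual debriefing. It says nothing about returning a questionnaire. Stages 1 and 2 also describe active efforts to reach and involve the most affected.
- **That IES-R is protected and only the other three outcomes are exposed.** The IES-R model is described only as confounder adjustment. If it models change, or T1 alone, it drops the same people. IES-R also has the same paired and McNemar tests.
- **That the results will be biased, and towards less improvement.** No loss rate is given, and the little-affected could equally be those who do not reply. For the same reason, the bias cannot be dismissed as conservative.

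It is also fair that effectiveness is a secondary objective, that the article's own limitations say the uncontrolled design prevents definitive inference on effectiveness, and that paired t and McNemar tests are standard for a pre/post design. These points lower the priority but do not remove the case for a better method.

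**Conclusion.** The point holds as an inexpensive improvement to a stated analysis choice, of moderate to low priority. As written, every test of change named for DES-IV, professional impact and P3SP uses only staff with both records, and the IES-R model is not specified well enough to say that it does otherwise.

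The size is conditional. At an assumed 20% T1 loss, the bias is 0.075 to 0.175 SD for a 1 SD difference at T0, or about 0.09 SD for a difference of about 0.7 SD at correlation 0.5. The sign depends on who is lost. These figures assume equal SDs at the two times and loss that depends on T0 score only. The documents neither establish nor exclude such loss.

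**What to change.** 1. **Total scores.** For all four, IES-R included, name as the main analysis a linear mixed model with T0 and T1 both as outcome rows, a time effect, a person random effect and institution as a fixed effect. Fit it by likelihood to all available records. Only five implementations are planned, so a random institution effect would be poorly estimated. The planned IES-R covariates can be kept.
2. **Cut-off outcomes.** Use a logistic mixed model with the same structure. Unweighted GEE is not an adequate substitute, because it generally needs loss to be completely at random and so does not cure loss that depends on T0.
3. **Sensitivity checks.** Keep the paired t, matched rank and McNemar tests, labelled as complete-pair analyses.

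The cost is a few sentences and some R code, with no new data. The downside is reliance on the model and on missingness at random: if loss depends on the unseen T1 state, the mixed model is biased too. Comparison with the complete-pair results shows how much the choice matters, but it does not test that assumption.
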